#### Control intervention

In the control group, wounds will not be surgically irrigated according to the NICE guideline recommendations [10].

### Permitted and not permitted medication(s)/treatment(s)

No additional study-specific treatments will be performed within the trial. Antibiotic treatment 5 days prior to surgery is an exclusion criterion. Preoperative antibiotic treatment due to septic peritonitis is allowed, but has to be recorded in the electronic case report form (eCRF). Application and timing of routine intraoperative antibiotic prophylaxis will be recorded in the eCRF. If indicated for medical reasons, all kinds of medication are permitted during the trial. Postoperative administration of antibiotics or medication with adverse effects on wound healing (e.g. immunosuppressive agents) will be recorded in the eCRF.

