### Randomization and blinding

Prior to inclusion in the trial, a GCP-certified investigator will perform the screening and collect detailed information from the patients and will obtain their written informed consent. An online tool of the Munich Centre of Clinical Trials (*Münchner Studien Zentrum* (MSZ)) will be used to generate the allocation sequence. This online tool uses pre-defined randomization lists, which will be created block-wise at the Institute of Medical Statistics and Epidemiology (*Technische Universität München* (TUM)) and will be stratified by study centre and level of contamination of the surgical procedure (class II–IV; Table 2).

A member of the study team will perform randomization during surgery after closure of the abdominal fascia is completed and will inform the surgical team of the assigned treatment. To assure balanced group sizes in the course of the accrual, a block-wise randomization is applied. Baseline characteristics of the patient and day of randomization must be documented on the printed randomization sheets. Subsequently, randomization sheets must be stored away from the patient records and trial documents to ensure blinding. The surgical team cannot be blinded, as no irrigation is used in the control group. However, patients, outcome assessors, and the trial statistician will be blinded for the trial intervention. The primary endpoint (SSI up to postoperative day 30) will be assessed clinically by a member of the local study team who will neither be part of the surgical team that performs the intervention nor have access to the randomization results in order to comply with observer-blinding. In addition, wound photographs will be taken at each study visit and evaluated via a central database by independent outcome assessors at spatially separated participating study sites. Unblinding of the local principal investigator is permissible if significant hazards for subjects’ safety or welfare occur.

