### Data collection and management

The applicable local regulations of data privacy protection will be followed. Prior to inclusion, patients will be informed that any patient-related data and materials will be appropriately pseudonymized and that these data may be used for analysis and publication purposes, pursuant to GCP regulations. All trial data will be recorded in eCRFs in a central database of the MSZ (MACRO™ version 3, Microsoft SQL Database, using Microsoft Internet Explorer version 6 or higher). After inclusion, baseline data (demographical data, medical history including history of SSI and history of radio/chemotherapy, concurrent medication, body mass index (BMI), ASA score, smoking/alcohol use, length of preoperative hospital stay, National Nosocomial Infection Surveillance (NNIS) risk score) will be documented accordingly. A physical examination will be performed and a blood sample will be taken (see Fig. 2 for included parameters). In the case of women of child-bearing potential, a pregnancy test will be additionally performed. Randomization will take place at the end of surgery after closure of the abdominal fascia when the level of contamination is definitely determined by the surgeon. Documented parameters of the surgical procedure include the administration and timing of antibiotic prophylaxis, the type and duration of the respective surgical procedure, the level of contamination according to CDC classification after closure of the abdominal fascia, the creation of an enterostomy, the intraoperative use of wound edge protectors and prophylactic changing of gloves during the operation, the wound closure technique, and the used suture material. Postoperatively, the local study personnel will perform six study visits. Wounds will be examined according to the CDC criteria for SSI, photographs will be taken at each visit, and between visits 4 and 6 one more routinely obtained blood sample will be analysed. In case of SSI, an additional microbiological swab will be taken from the wound. Postoperative medication with adverse effects on wound healing or antibiotics will be recorded in the eCRF.

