#### Supportive analysis of the primary endpoint

Randomization will be stratified by study centre and level of contamination. Supportive analysis of the primary endpoint will be performed using a binary logistic regression model with dependent variable SSI and the covariates treatment group, study centre, and level of contamination. In addition, the following parameters might influence the outcome which is why they will be included as model covariates:Operation-related risk factors: (a) type of surgery; (b) duration of surgery; (c) use of wound-edge protectors; (d) intraoperative changing of gloves before skin closure; (e) presence of an enterostomy; (f) administration and timing of antibiotic prophylaxis; (g) NNIS risk score;Patient-related risk factors: (h) BMI; (i) ASA score; (j) age; (k) diabetes; (l) duration of preoperative hospital stay; (m) smoking; (n) alcohol abuse; (o) history of SSI; (p) history of radio- and/or chemotherapy.

Furthermore, surgical and patient characteristics will be monitored to identify other potential confounders and to allow adjustment for these variables.

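### The supportive SSI model adjusts for duration of surgery and glove change, both of which can be determined after the surgical team learns the arm

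*Protocol article*

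**What the plan says.** **Timing of allocation.** Under Randomization and blinding, a study team member is to "perform randomization during surgery after closure of the abdominal fascia is completed and will inform the surgical team of the assigned treatment". The same section adds: "The surgical team cannot be blinded, as no irrigation is used in the control group". The local assessor, by contrast, will "neither be part of the surgical team that performs the intervention nor have access to the randomization results".

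**What follows allocation.** Under Interventions, the PHX and saline arms each receive a 1000 ml irrigation with suction before skin closure. The control arm receives none.

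**What the model adjusts for.** Supportive analysis of the primary endpoint fixes a logistic model with treatment group, centre, contamination level and a list of further covariates. Item (b) of the operation-related factors is duration of surgery. The list continues with "d) intraoperative changing of gloves before skin closure; (e) presence of an enterostomy; (f) administration and timing of antibiotic prophylaxis".

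**How the items are recorded.** Data collection and management documents the duration of the procedure without saying when it ends. It documents glove change as "prophylactic changing of gloves during the operation", without timing relative to randomization.

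**Co-treatment.** Under Permitted and not permitted medication(s)/treatment(s): "If indicated for medical reasons, all kinds of medication are permitted during the trial", and "Postoperative administration of antibiotics or medication with adverse effects on wound healing (e.g. immunosuppressive agents) will be recorded in the eCRF". Postoperative antibiotics are not on the covariate list.

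**The concern.** A covariate is safe to adjust for when the assigned arm cannot have influenced it. Two listed covariates may fail that test. Skin closure comes after the arm is disclosed, so a glove change described as "d) intraoperative changing of gloves before skin closure" may be made by a team that already knows the allocation. Duration of surgery, if it runs to skin closure, includes irrigation time in two arms and none in the third.

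If either item is partly a result of the arm, the adjusted treatment coefficient no longer estimates the effect of assignment. The supportive model would then differ from the primary result for a reason unrelated to chance imbalance, and a reader could not tell which of the two explains the gap. If the eCRF does not separate what happened before allocation from what happened after, no later analysis plan can recover it.

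**Working it through.** **1. Order of events, from the article.** Incision; procedure; fascia closure, with contamination level settled; randomization; arm disclosed to the surgical team; irrigation (PHX and saline arms only); skin closure. Contamination level, BMI, ASA score and age are fixed before randomization. A glove change placed only ahead of skin closure, and a duration with no stated end point, can fall on either side of it.

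**2. Duration, in algebra.** Let A = 1 for PHX and 0 for no irrigation, D the incision-to-fascia-closure time, t the minutes that irrigation adds (taken as constant), β the log odds of SSI per minute of surgery and θ the arm effect given D.
- Model on pre-randomization time: logit p = a + θA + βD.
- Recorded total time: T = D + tA, so D = T − tA.
- Substituting: logit p = a + (θ − βt)A + βT.

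The model adjusted for total duration therefore reports θ − βt. If the added minutes themselves raise risk at rate β, the total arm effect is the direct effect plus βt, and the model again reports it less βt.

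If longer operations carry more risk (β > 0), the shift makes PHX look better against no irrigation. For PHX against saline it cancels when irrigation takes equally long in both arms.

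**3. Size.** With h the odds ratio per hour of surgery, the reported odds ratio is the correct one multiplied by h^(−t/60). The article gives neither t nor h. The Discussion cites a contact time of 10–15 min for PHX. Assuming that this whole time lengthened the operation, the factor lies between h^(−10/60) = h^(−1/6) and h^(−15/60) = h^(−1/4). If contact time runs on while the skin is closed, t is smaller and the factor is nearer 1. No numerical bias can be claimed.

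**4. Glove change.** If the arm influences it, adjustment removes whatever part of the arm difference passes through it. If an unrecorded judgement about the wound also drives it, adjustment can create an association that randomization had excluded. The article supports neither a direction nor a size.

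**5. Co-treatment and power: illustration only.** First, the plan's own figures: exact enumeration at SSI rates of 2.2%, 8.7% and 16.2% gives 94.9% (equal-tailed Fisher) or 96.5% (probability-ordered) for test 1, against 94% stated, and 85.4% for test 2, against 85% stated. Now assume a co-treatment with relative risk RR, used d more often in the comparator arms. The comparator rate becomes base × [1 − d(1 − RR)]. Probability-ordered power:

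| RR, d (assumed) | Control rate | Saline rate | Test 1 | Test 2 |
|---|---|---|---|---|
| none | 16.2% | 8.7% | 96.5% | 85.4% |
| 0.7, 10 points | 16.2 × 0.97 = 15.7% | 8.7 × 0.97 = 8.4% | 95.6% | 82.9% |
| 0.5, 40 points | 16.2 × 0.80 = 13.0% | 8.7 × 0.80 = 7.0% | 86.9% | 63.1% |

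In the opposite direction, with no PHX effect and the extra use in the PHX arm, rejection rises from 2.0% to at most 6.1% (test 1) and from 3.5% to at most 7.9% (test 2). RR, d and the direction have no source in the article.

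**The case against.** The strongest reply is that little depends on this model. The confirmatory tests are unadjusted Fisher tests on the intention-to-treat set, and the logistic regression is only supportive. The article calls glove change and duration operation-related risk factors, never baseline values, and does not say that gloves are changed after allocation or that duration runs to skin closure. The case report form may already define both safely. All of this is fair, and it limits the point to the supportive estimate. It does not remove it, because the article commits to these covariates without fixing when they are measured.

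A reader might infer something stronger: that surgeons who know the arm could compensate with postoperative antibiotics and shift the SSI rate unseen. The article does not support that.
- Antibiotic use is recorded and can be tabulated by arm. Whether it will be is reporting detail that an article may leave to the full protocol or analysis plan.
- The article does not say who prescribes postoperatively or whether they know the arm.
- Compensation for an unirrigated wound would not carry over to the saline arm, which is irrigated. The largest power loss in the illustration, for test 2, therefore has no mechanism behind it.
- Discretionary medication fits a pragmatic design, and leaving postoperative antibiotics out of the model is defensible: they arise after allocation, and some will treat an SSI already counted.

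Blinded assessment and central photograph review guard against detection bias, not against differing co-treatment. That possibility stays open, but it is not shown.

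**Conclusion.** The point holds for the supportive model only. As written, the plan adjusts for two items that may be determined after the arm is disclosed, and one of them, duration, may include time that only the irrigated arms spend. The supportive estimate can then be biased. For duration the shift is −βt on the log-odds scale in PHX versus no irrigation, with β and t unknown; for glove change neither sign nor size can be given.

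This rests on two conditions that the article leaves open: that duration runs past randomization, and that at least some glove changes follow it. If both are measured before allocation, the problem disappears.

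The primary Fisher tests, the sample size and the stated power are unaffected. The co-treatment power figures are illustrative and should not be cited as a consequence of the plan.

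**What to change.** - **eCRF:** record incision-to-fascia-closure time, and whether gloves were changed before or after randomization.
- **Supportive model:** replace total duration with incision-to-fascia-closure time, and glove change with change before randomization. Alternatively, drop both covariates.
- **Adjustment set:** state that items arising after randomization, including postoperative antibiotics actually given, will not be used for adjustment. Apply this also to the provision at the end of that section for adjusting for further confounders.
- **Description by arm only:** glove change after randomization, and postoperative antibiotics with those given for an SSI shown separately.

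The cost is one or two extra eCRF fields, completed when the contamination level has to be settled for stratification anyway. The fields need to be in place before recruitment, because the timing cannot be reconstructed reliably afterwards. No clinical rule changes.

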### Risks

No additional risks for study patients are anticipated, since IOWI with PHX or saline, as well as the control intervention, represent clinically established standard methods. PHX 0.04% irrigation solution is approved for surgical wound irrigation of soft tissue wounds in Germany. The study will be planned, conducted, and analysed according to all relevant national and international rules and regulations (AMG [20], ICH-GCP [21], Declaration of Helsinki [23]). The safety of PHX solutions has been demonstrated in marketing studies. However, adverse effects may only be expected in the improbable event of accidental contamination of the respective irrigation solutions or in case of unknown hypersensitivity to PHX. The potential benefits of a reduced risk of SSI outweigh the mentioned negligible potential adverse effects of PHX. The safety of the subjects is ensured by regular study visits, enforcing GCP guidelines. Furthermore, each patient will be provided with insurance coverage for any potential harm from trial participation.

### Data collection and management

The applicable local regulations of data privacy protection will be followed. Prior to inclusion, patients will be informed that any patient-related data and materials will be appropriately pseudonymized and that these data may be used for analysis and publication purposes, pursuant to GCP regulations. All trial data will be recorded in eCRFs in a central database of the MSZ (MACRO™ version 3, Microsoft SQL Database, using Microsoft Internet Explorer version 6 or higher). After inclusion, baseline data (demographical data, medical history including history of SSI and history of radio/chemotherapy, concurrent medication, body mass index (BMI), ASA score, smoking/alcohol use, length of preoperative hospital stay, National Nosocomial Infection Surveillance (NNIS) risk score) will be documented accordingly. A physical examination will be performed and a blood sample will be taken (see Fig. 2 for included parameters). In the case of women of child-bearing potential, a pregnancy test will be additionally performed. Randomization will take place at the end of surgery after closure of the abdominal fascia when the level of contamination is definitely determined by the surgeon. Documented parameters of the surgical procedure include the administration and timing of antibiotic prophylaxis, the type and duration of the respective surgical procedure, the level of contamination according to CDC classification after closure of the abdominal fascia, the creation of an enterostomy, the intraoperative use of wound edge protectors and prophylactic changing of gloves during the operation, the wound closure technique, and the used suture material. Postoperatively, the local study personnel will perform six study visits. Wounds will be examined according to the CDC criteria for SSI, photographs will be taken at each visit, and between visits 4 and 6 one more routinely obtained blood sample will be analysed. In case of SSI, an additional microbiological swab will be taken from the wound. Postoperative medication with adverse effects on wound healing or antibiotics will be recorded in the eCRF.

To promote complete follow-up, patients that have already been discharged from the hospital by the time of the study visits will be supported in arranging transport and expenses necessary to ensure participant retention. If, however, the patient is unable to attend visit 8 due to postoperative treatment in a rehabilitation facility or other medical reasons, a standardized protocol for evaluation and documentation of the wound (including wound photograph) will have to be filled out by the treating physician and sent to the coordinating study site for independent evaluation.

At the end of the clinical study all study-relevant data must be archived for at least 10 years. Patient identification lists and patient files are retained in the respective study sites separately. The infrastructure and the personnel for the data management will be provided by the Data Management Centre at the MSZ, a member of the German Network of Coordinating Centres for Clinical Trials (*Koordinierungszentren für Klinische Studien* (KKS)). The eCRFs are checked for completeness, plausibility, and correctness at entry. The investigator is responsible for the accuracy and verifiability of each entry. Validating programmes as well as individual inspection of data through the MSZ will ensure completeness, validity, and plausibility. Each remaining question or missing response is documented through data clarification requests, to which the local investigator is obliged to respond as quickly as possible.

### Access to data and dissemination of results

Only the sponsor, personnel authorized by the sponsor, and the trial statistician will have access to the final dataset. After completion of the clinical study, the sponsor-delegated coordinating investigator will prepare a multicentre manuscript of the study results for publication in a reputable scientific journal. Authorship eligibility will be regulated in the Clinical Trial Agreement for all study sites. The publication of the principal results from any single-centre experience within the trial is not allowed until the preparation and publication of the multicentre results.

### Monitoring

Monitoring will be performed by the MSZ, an institution experienced in the monitoring of multicentre, surgical RCTs, in order to guarantee high quality of the study conduct and data retrieval. Monitoring will be carried out in accordance with ICH-GCP guidelines [21]. Monitors will visit all participating centres on a regular base, starting with an initiation visit at each site. Furthermore, close-out visits are planned for each centre. A monitoring manual describing the scope of the monitoring activity in detail will be provided. The monitor is authorized to compare trial documents and original data in adherence to data protection rights. The investigator provides direct access to patient’s documents/original source data to the monitor at any time. The monitor will also contact all participating centres and the sponsor on a regular basis. Furthermore, the sponsor and the competent health authorities have the right to audit/inspect the trial sites involved in the trial as part of quality assurance according to GCP regulations.

### Safety evaluation and reporting of adverse events

All AE/SAEs from the moment of randomization until the last study visit have to be assessed, documented, and reported by the local principal investigator or designated sub-investigator. SSIs and all other local wound complications and surgical complications will be documented as AE/SAE, as well as their severity and the consequent treatment according to the Clavien Dindo Classification (Table 3). SAEs have to be reported within 24 h and will be classified by intensity, outcome, and causality. All SAEs will be subject to a second assessment by a designated person who will be independent from the reporting investigator and the trial sponsor. Pursuant to AMG and GCP regulations, the ethics committee and the competent federal authority will be informed of all suspected unexpected serious adverse reactions (SUSARs) and all SAEs resulting in death or that are life threatening during the trial. In addition, an independent Data and Safety Monitoring Board will address patient safety and assess regular safety reports for any termination criteria.

### Statistical methods

The statistical analysis will be conducted by a group allocation-blinded statistician from the Institute for Medical Statistics and Epidemiology of the TUM, in line with the ICH-GCP guidelines [21]. For the statistical analysis, SAS software version 9.2 or higher will be used (SAS Institute Inc., Cary, NC, USA).

#### Sample size calculation

The sample size was calculated (nQuery Advisor software version 7.0, Statistical Solutions Ltd, Cork, Ireland) based on the primary endpoints of the study, assuming SSI rates of 2.2% in the PHX group (according to the trial by Roth et al. [17]), 8.7% in the saline group (according to the results of the trial by Cervantes-Sanchez et al. [15]) and 16.2% in the control group (according to results of the meta-analysis by Mueller et al. [14]). The global significance level was set to 5%. Since the PHX arm will be used twice for a comparison, the Bonferroni-Holm procedure was used to set the local alpha level to 2.5% for test 1 (PHX versus no irrigation) and to 5% for test 2 (PHX versus saline). If 230 patients are recruited in the PHX arm, 230 patients in the saline arm, and 80 patients in the control arm (a total of 540 patients), the two-sided Fisher exact test will have a power of 94% for test 1 and 85% for test 2 to detect differences between the treatment groups. The comparison of saline irrigation versus control is not included in the sample size calculation as it will not be analysed in a confirmatory manner; the low medical interest cannot justify the large increase in patient numbers.

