**Discussion:**

The IOWISI trial will provide high-level evidence as a basis for clinical recommendations regarding the use of IOWI with PHX or saline and will potentially impact on future clinical guidelines and practice. The pragmatic trial design guarantees high external validity.

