### Objective

The IOWISI trial aims to investigate if IOWI with PHX solution (0.04%) or saline (NaCl 0.9%) can reduce the rate of postoperative SSI within 30 days (according to the CDC definition [19]; Table 1) after laparotomy for visceral surgery. The results of the IOWISI trial will provide high-level evidence for future clinical recommendations regarding the use of IOWI in visceral surgery by laparotomy and provide the participating patients the opportunity of a potentially improved treatment.

**Table 1 Tab1:** Definition and classification of surgical site infection (SSI) [19]

Superficial incisional SSI	Infection occurs within 30 days after the operation and infection involves only skin or subcutaneous tissue of the incision and at least *one* of the following: • Purulent drainage, with or without laboratory confirmation, from the superficial incision. • Organisms isolated from an aseptically obtained culture of fluid or tissue from the superficial incision. • At least one of the following signs or symptoms of infection: pain or tenderness, localized swelling, redness, or heat *and* superficial incision is deliberately opened by surgeon, *unless* incision is culture-negative. • Diagnosis of superficial incisional SSI by the surgeon or attending physician. Notes: Do *not* report the following conditions as SSI: • Stitch abscess (minimal inflammation and discharge confined to the points of suture penetration).
Deep incisional SSI	Infection occurs within 30 days after the operation and the infection appears to be related to the operation and infection involves deep soft tissues (e.g. fascial and muscle layers) of the incision and at least *one* of the following: • Purulent drainage from the deep incision but not from the organ/space component of the surgical site. • A deep incision spontaneously dehisces or is deliberately opened by a surgeon when the patient has at least one of the following signs or symptoms: fever (>38 °C), localized pain, or tenderness, unless site is culture-negative. • An abscess or other evidence of infection involving the deep incision is found on direct examination, during reoperation, or by histopathologic or radiologic examination. • Diagnosis of a deep incisional SSI by a surgeon or attending physician. Notes: • Report infection that involves both superficial and deep incision sites as deep incisional SSI. • Report an organ/space SSI that drains through the incision as a deep incisional SSI.

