After closure of the abdominal fascia according to local standards, laparotomy wounds will either be irrigated with PHX or saline. The volume of 1000 ml was chosen to be sure that large laparotomy wounds would be sufficiently irrigated. This was determined by the clinical experience of senior surgeons at our institution since, so far, no recommendations for the optimal volume of surgical wound irrigation exist. The same applies to the duration and technique of irrigation. However, the POLIS pilot trial compared “short” versus “long” irrigation with PHX and no differences in SSI rates were observed [18]. In vitro experiments show that a contact time of 10–15 min is required for PHX to act fully [12]. To ensure this, the irrigation technique will be standardized in the IOWISI trial. In addition, wounds will be left moistened with the PHX solution at the end of the irrigation and shall not be rubbed dry with abdominal cloths or rinsed with saline again.

The primary endpoint is the incidence of SSI 30 days postoperatively, according to the widely accepted CDC definition and classification (Table 1) [19]. Since many different SSI definitions have been proposed over the past decades, standardized reporting is crucial for the comparability of trials regarding SSI prevention.

The results of this pragmatic trial will provide high-level evidence for clinical recommendations regarding the use of IOWI with PHX or saline to prevent SSI after laparotomy, potentially impact future clinical guidelines and provide participating patients the opportunity of an improved treatment.

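### The stated aim and conclusions cover saline irrigation, but saline versus no irrigation is non-confirmatory and has about 42% power at the planning rates

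*Protocol article*

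**What the plan says.** All references are to the protocol article.

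- **Objective (Background):** the trial "aims to investigate if IOWI with PHX solution (0.04%) or saline (NaCl 0.9%) can reduce the rate of postoperative SSI within 30 days".
- **Abstract, Discussion paragraph:** the trial "will provide high-level evidence as a basis for clinical recommendations regarding the use of IOWI with PHX or saline".
- **Closing paragraph of the Discussion:** "The results of this pragmatic trial will provide high-level evidence for clinical recommendations regarding the use of IOWI with PHX or saline".
- **Analysis of the primary endpoint measure:** two hypotheses only, PHX versus no irrigation (test 1) and PHX versus saline (test 2). Both are two-sided Fisher exact tests under Bonferroni-Holm at a global 5%.
- **Sample size calculation:** saline versus control is left out because "it will not be analysed in a confirmatory manner; the low medical interest cannot justify the large increase in patient numbers". The planned allocation is "230 patients are recruited in the PHX arm, 230 patients in the saline arm, and 80 patients in the control arm". No power is given for saline versus control.

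**The concern.** Whether saline reduces SSI can be tested directly only against no irrigation. PHX versus saline ranks the two solutions; it does not show whether saline is better than doing nothing. The aim and the two concluding statements therefore reach further than the confirmatory tests.

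The reason given, low medical interest, also sits poorly with the rest of the article. The Rationale describes guidelines that differ on irrigation and rest on weak evidence. Previous trials reports a single standardized RCT of saline against no irrigation. The Discussion calls for RCTs to settle equipoise about saline as well as antiseptics. The Interventions section labels saline an experimental group.

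At stake is what the trial may conclude about saline. A non-significant difference would say little at this power, and a nominally significant one would lie outside the two tests that the 5% global level covers. Neither is a firm basis for a recommendation on saline.

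**Working it through.** **Inputs, all from Sample size calculation unless noted**

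- SSI rates: "assuming SSI rates of 2.2% in the PHX group", "8.7% in the saline group" and "16.2% in the control group".
- Arm sizes: 230 PHX, 230 saline, 80 no irrigation.
- Test: two-sided Fisher exact, 2.5% for test 1 and 5% for test 2.
- Dropout: 8–10% (Sensitivity of the primary endpoint measure).
- Level for saline versus no irrigation: 5%. This is an assumption. The article gives that level for exploratory tests only under secondary endpoints.

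**Step 1: reproduce the stated power.** Exact power is the sum, over all pairs of event counts, of the product of the two binomial probabilities wherever the Fisher p-value is at or below the level. The two-sided p-value is formed either by probability ordering or by doubling the smaller tail.

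| Comparison | Stated | Probability-ordered | Doubled tail |
|---|---|---|---|
| Test 2 (2.2% of 230 vs 8.7% of 230, 5%) | 85% | 85.4% | 85.4% |
| Test 1 (2.2% of 230 vs 16.2% of 80, 2.5%) | 94% | 96.5% | 94.9% |

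A continuity-corrected normal approximation gives 93.3% for test 1. The stated figures are reproduced within the spread of standard methods.

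**Step 2: same method for saline versus no irrigation, 5%**

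| Scenario | Probability-ordered | Doubled tail |
|---|---|---|
| 8.7% of 230 vs 16.2% of 80 | 41.9% | 36.8% |
| 8% dropout (212 vs 74) | 38.8% | 34.3% |
| 10% dropout (230 × 0.9 = 207 vs 80 × 0.9 = 72) | 37.9% | 33.2% |

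Normal approximations give 39.7% (continuity-corrected) and 47.0% (uncorrected), so the range across standard variants at full enrolment is 37–47%.

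**Step 3: expected precision.** SE of the difference = √(0.087 × 0.913/230 + 0.162 × 0.838/80) = √(0.000345 + 0.001697) = 0.0452. The planned difference is 16.2 − 8.7 = 7.5 points. The 95% CI centred on it is 7.5 ± 1.96 × 4.52 = 7.5 ± 8.9, or about −1.4 to +16.4 points. It includes zero even when the observed difference equals the planned one.

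**Step 4: dependence on the control rate.** The Rationale cites SSI rates from 14.5% to 25.0%, and the appendectomy trial that supplied the 8.7% had 25% without irrigation (Previous trials). With saline held at 8.7% and 230 vs 80 patients:

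| Control rate | Power |
|---|---|
| 14.5% | 28% |
| 16.2% (planning rate) | 42% |
| 20% | 71% |
| 25% | 93% |

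**Step 5: what adequate power would cost.** For 80% power at the planning rates, the Fisher test needs about 325 patients per arm, or about 540 controls if saline stays at 230. The sponsor's point about a large increase in patient numbers is correct.

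**Step 6: a gated third test.** Suppose saline versus no irrigation is tested at 5% only when Bonferroni-Holm has rejected both PHX hypotheses. Any false rejection of the third hypothesis then needs either a prior false rejection, which Holm already controls at 5%, or two true PHX differences, in which case the full 5% is free for the last test. The familywise level stays at 5%. At the planning rates, all three tests are significant in about 32% of trials (32.4% by simulation). If PHX and saline both had a rate of 8.7%, the gate would open in about 1.4% of trials.

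**The case against.** The strongest reply is that this is a disclosed priority, not a gap. The abstract, the sample size section and the analysis section all name the same two confirmatory tests, and the sample size section says openly what is left out and why. The low power is an accepted consequence, and no stated power figure is wrong. This stands: the fault lies in the aim and conclusions, not in the testing plan.

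The two concluding statements can also be read more narrowly. They speak of recommendations on using PHX or saline, and the confirmatory PHX versus saline test, with a stated 85% power, bears on which solution to use. An aim to investigate can be met by an exploratory analysis. This stands in part. The Objective, however, asks whether saline can reduce SSI, and PHX versus saline cannot answer that.

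A reader might infer that half of the trial's question cannot be answered, or that the trial will say nothing useful about saline. The documents do not support either reading. The arms are randomized, so an unbiased estimate with a confidence interval is available, and power would reach 93% if the control rate were 25%. Nor do the documents plan a confirmatory claim about saline, so the plan does not breach its own 5% global level. How a saline result would later be reported is conjecture.

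Finally, the gated step helps least where PHX and saline work equally well, because PHX must first beat saline. That limits the remedy, but the step is still free.

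**Conclusion.** The point holds as a mismatch between the stated aim and conclusions and what the design can confirm. At the planning rates, full enrolment and a two-sided 5% level, saline versus no irrigation has about 42% power (37–47% across standard methods), and about 38% after 10% dropout. Over the control rates that the article itself cites, power runs from 28% to 93%, so the shortfall depends on the planned 16.2%. The trial can estimate saline's effect. It cannot support the announced claim about saline in a confirmatory way or, at its planning rates, with adequate power. The two PHX tests, their sample size and their error control are not affected. The change is worth making because patient numbers were part of the reason for ruling out confirmatory testing, and a last-step test needs no additional patients.

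**What to change.** 1. In the Objective, the abstract's Discussion paragraph and the closing Discussion, state that the confirmatory questions are PHX versus no irrigation and PHX versus saline. State that saline versus no irrigation will be reported as a risk difference with a 95% CI, and that a non-significant result will not be read as evidence that saline is ineffective.
2. Add one line to the analysis of the primary endpoint: if tests 1 and 2 are both rejected under Bonferroni-Holm, test saline versus no irrigation with a two-sided Fisher exact test at 5%. If the gate does not open, the comparison remains exploratory. The sentence in Sample size calculation that denies confirmatory status would need matching wording, noting that the step is not powered for.

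Cost: a few sentences, no alpha and no patients. The downside is a more modest stated objective. The third step succeeds in only about 32% of trials at the planning rates and is reached in about 1% if PHX and saline are equally effective (both 8.7%).
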